## Abstract

**Background:**

Sustained attention is a complex cognitive function required for the successful performance of tasks such as walking, cycling, driving, conversations and other prolonged tasks. Deficits of this function are associated with frailty, falls, and general cognitive decline in older adults. Sustained attention declines with age and is impaired in many neurological disorders. However, little is known about the underlying neurophysiological characteristics of sustained attention deficits in neurogeriatric patients and their interaction with other cognitive domains. Electroencephalography (EEG) provides a non-invasive and scalable method to assess neural dynamics with high temporal resolution. EEG parameters have shown promise as objective markers of cognitive dysfunction in aging and neurodegenerative conditions, but their specific relevance as surrogate markers of sustained attention in neurogeriatric patients remains unclear. Identifying reliable EEG-based surrogate markers could facilitate early detection, risk stratification, and targeted interventions. Therefore, this study aims to investigate EEG-based parameters as potential surrogate markers of sustained attention in neurogeriatric patients.

**Methods/design:**

The study “Studying Neurocognitive Systems for Sustained Attention in Neurogeriatrics Patients” (SENSE-AGE) is a prospective, explorative, observational study and will include 120 geriatric participants. At admission, participants will perform a Go-NoGo task, a Psychomotor Vigilance Task (PVT) and resting-state condition during EEG recording, using a 32-channel system. Task-based event-related potentials (ERPs) and frequency-band power will be extracted. Neuropsychological tests characterize global and domain-specific cognition and will examine associations between sustained attention, broader cognitive performance, and EEG parameters. Questionnaires will assess fatigue, sleep, health-related quality of life, and subjective cognition. A subgroup of 50 participants will be re-evaluated at the end of the inpatient stay, after 2–3 weeks of standardized geriatric complex treatment. The main hypotheses of the study are: sustained attention (i) correlates with ERP amplitude and latency; (ii) correlates with EEG power; (iii) improves after an inpatient multiprofessional complex treatment at both the task-performance and neurophysiological level.

**Discussion:**

The study protocol describes an experimental approach to investigate sustained attention in a neurogeriatric cohort combining a behavioral approach with EEG recordings. The results may help defining objective and quantitative surrogate markers of sustained attention in this vulnerable cohort.

## Introduction

1

Attention, one of the six central cognitive domains, is crucial for daily cognitive processing, enabling a selective focus on relevant environmental and internal information while suppressing distractions (Bergius, 2009; Falkai et al., 2018). Sustained attention, or vigilance, refers to the ability to maintain focus and process relevant information over time (Klösch et al., 2022). This type of attention is essential for maintaining safety and efficiency in tasks requiring prolonged attention, such as navigating traffic, responding to environmental changes (Yanko and Spalek, 2013; Walker and Trick, 2018; Park et al., 2021), and engaging in conversations (Sturm, 2008; Häusler and Sturm, 2009). Most interestingly, its decline with age is associated with reduced mobility (O’Halloran et al., 2011; O’Halloran et al., 2014), and increased risk of falls (O’Halloran et al., 2011; Bennett Murphy et al., 2001; Ganesh and Gurumoorthy, 2021). Moreover, sustained attention is affected in various neurological conditions, including Alzheimer’s dementia (AD) (Berardi et al., 2005; Huntley et al., 2017), dementia with Lewy bodies (Collerton et al., 2003; Hamilton et al., 2024), Frontotemporal dementia (O’Keeffe et al., 2007), and Parkinson’s disease (PD), even at early stages (Pfeiffer et al., 2014; Agosta et al., 2020). For example, the prevalence of AD increases from 0.6% in individuals aged 65–69 years to more than 22% in those aged 90 years and older (Lobo et al., 2000), and mild cognitive impairment (MCI) occurs in approximately 40% of patients with PD (Dorsey et al., 2018). These disorders often manifest as reduced peripheral nerve signal quality (Anderton, 2002), slower brain processing (Salthouse, 2016), and diminished compensatory capacity (Bunzeck et al., 2024), suggesting that geriatric patients are at particularly increased risk of suffering from sustained attention deficits. The potential for treating these deficits in geriatric patients and the impact on other cognitive functions and neurophysiological patterns remain underexplored, partly reflected in limited availability of validated and clinically applicable objective markers of sustained attention (Fortenbaugh et al., 2017; Huang et al., 2023).

Although several neural networks have been identified as potentially relevant in sustained attention, including the default mode network, the frontoparietal network, the salience network, and the locus coeruleus norepinephrine system (Bonnelle et al., 2011; Smith et al., 2011; Langner and Eickhoff, 2013; Buckner and DiNicola, 2019; Slattery et al., 2022), the interaction of these systems and their contribution to age-related or clinical sustained attention deficits remain incompletely understood (Fortenbaugh et al., 2017; Huang et al., 2023). Neuropsychological and neuroimaging studies have identified specific brain regions as being associated with sustained attention, including the anterior cingulate cortex, dorsolateral prefrontal cortex, and parietal regions, predominantly in the right hemisphere (Staub et al., 2013). EEG research further indicates age-related alterations in attentional processing. Older adults may exhibit increased frontal activation during cognitive control tasks, possibly reflecting compensatory recruitment (Hong et al., 2016). In addition, reductions in P300 amplitude, prolonged latencies, and alterations in theta and alpha oscillatory dynamics have been described, suggesting changes in attentional resource allocation and processing speed (Finnigan and Robertson, 2011; Vaden et al., 2012; Staub et al., 2014). However, most evidence derives from healthy populations, and comparatively little is known about the neural dynamics of sustained attention in geriatric patients.

Several psychological theories have been proposed to explain sustained attention deficits. The resource depletion theory posits that sustained attention deficits result from a limited information processing capacity due to an individually perceived high task load (Caggiano and Parasuraman, 2004; Warm et al., 2008; Thomson et al., 2015). The mind-wandering theory postulates that a low task load results in attention drifting, thereby increasing the likelihood of mind-wandering (Randall et al., 2014). The resource control theory synthesizes the aforementioned theories, proposing that fixed attentional resources are depleted by mind-wandering and that reduced executive control over time is a consequence of this depletion (Thomson et al., 2015). All of these theories conceptualize sustained attention deficits as a form of cognitive performance loss during the sustained attention task.

The findings of Pershin et al. (2023) challenge the existing theories by suggesting that changes in sustained attention are less related to the actual performance of a sustained attention task, but are instead more closely associated with phases between subsequent trials in such task—which they describe as recovery phases. They demonstrated that electrophysiological markers such as alpha power changes within the sustained attention task, exhibited the greatest observed changes during intertrial intervals, where no response was required. This suggests that these intervals may represent phases when the brain is recovering from task-related demands (Pershin et al., 2023). We suggest that increased stress levels, which may occur when cognitive tasks require more “brain effort” in older adults, could further exacerbate sustained attention deficits by disrupting recovery phases, leading to a vicious cycle of reduced attention and increased stress (Selye, 1978; Wippert et al., 2009; McAvinue et al., 2015; Dillard et al., 2019; Luna et al., 2022; Buzsáki et al., 2003).

The combination of psychometric tests and EEG enables the concurrent evaluation of the correlation between behavioral responses and neural activity (Olbrich et al., 2015). In a general sense, EEG can be analyzed along the time domain and the frequency domain. Previous research has employed EEG parameters to investigate temporal differences in processing and responding to stimuli during sustained attention tasks. Event-related-potential (ERP) latency and amplitude parameters, as well as power changes in the alpha and theta bands, are directly related to attentional performance in older adults (Finnigan and Robertson, 2011; Vaden et al., 2012; Staub et al., 2014; Getzmann et al., 2016).

In the frequency domain, spectral analysis entails the examination of the power of predefined frequency bands, which are associated with discrete cognitive processes. For example, global alpha power and frontal-parietal theta power have been demonstrated to be associated with attention (Huizeling et al., 2021; Griggs et al., 2023). Studies on sustained attention and vigilance in younger healthy adults have indicated that there are increases in fronto-medial theta and global alpha power over time-on-task (Oken et al., 2006; Kamzanova et al., 2014; Clayton et al., 2015; Huang et al., 2023; Pershin et al., 2023), which may be indicative of increased attentional disengagement (Wascher et al., 2018) due to a reduction in information processing and cognitive resources (Pershin et al., 2023). Importantly, oscillatory dynamics have also been directly linked to behavioral performance. Persons with higher resting alpha power (∼10 Hz) showed larger late positive ERPs and better sustained attention performance (Dockree et al., 2007). However, opposite results may arise in task-related alpha modulation. Theta power showed positive correlation with task difficulty across age groups (Pergher et al., 2019).

In the time domain, ERPs reflect changes in cortical electrical activity in response to events or in relation to actions. ERPs can provide insights into the temporal course of cognitive processes. In sustained attention tasks, ERPs such as the N200 and P300 components, appear approximately 200–300 ms after a stimulus, respectively (Patel and Azzam, 2005). The N200 component is associated with stimulus detection and early attentional control (Patel and Azzam, 2005), as well as inhibitory and attentional processes (Warchoł and Zaja̧c-Lamparska, 2023). The P300 is associated to attentional processing and stimulus relevance (Polich, 2007; Staub et al., 2014), both have been associated with age-related neurocognitive functioning. Empirical evidence indicates that better sustained attention performance is associated with larger P300 amplitudes and shorter P300 and N2 latencies, whereas reduced amplitudes and prolonged latencies are linked to poorer performance (Finnigan and Robertson, 2011; Staub et al., 2014). Higher N2 amplitudes have been observed in high-performing individuals, suggesting more efficient stimulus evaluation and inhibitory control (Ramos-Loyo et al., 2004). The N200 appears to be reduced in older adults (Patel and Azzam, 2005) and in people with MCI and AD, at least in visual attention tasks (Morrison et al., 2018). The P300 also shows reduced amplitude and increased latency in older adults, indicating slower cognitive processing and reduced attentional resources (Chiang et al., 2018; Morrison et al., 2018; Chiang et al., 2024). Given the age-related changes in the N200 and P300 components (Riis et al., 2008; Van Dinteren et al., 2014; Chiang et al., 2018) and their increased prevalence in neurological disorders such as PD (Xu et al., 2022) and AD (Chiang et al., 2018), we will examine whether comparable electrophysiological patterns can be observed in a clinically heterogenous, neurogeriatric inpatient cohort, and how they relate to sustained attention performance.

Given the critical role of sustained attention in everyday life and the changes associated with aging, it is important to further investigate how sustained attention is reflected in EEG measures, including ERPs and power spectral changes in the frequency bands. Although these electrophysiological parameters have been associated with attentional processes, their clinical relevance as surrogate markers of sustained attention, particularly in neurogeriatric populations, remains insufficiently established.

Sustained attention in older populations is embedded within a broader biopsychosocial context. Sleep disturbances and poor sleep quality have been linked to reduced cognitive performance and reduced health-related quality of life (HrQoL) in aging cohorts (Costa et al., 2022; Sella et al., 2023). Affective symptoms such as depressive and anxiety states are associated with broad cognitive impairment, including reduced attentional control, executive functioning, memory and processing speed (Forbes et al., 2024). Moreover, subjective cognitive complaints (SCC) frequently diverge from objective measures but are clinically relevant for everyday functioning. Therefore, in addition to behavioral and electrophysiological measures, the present study includes assessments of fatigue, sleep quality, HrQoL and SCC to more comprehensively characterize sustained attention in aging.

The following research questions are thus defined for this study:

(i) Is there a correlation between sustained attention and ERPs, N200 and P300, of the EEG in latency and amplitude?

(ii) Is there a correlation between sustained attention and EEG power in the alpha and theta range? It will be tested if the correlations observed in the initial or final phases of the task differ from those observed over the entire task duration. Additionally, the hypothesis will be tested as to whether the correlation between SA and power varies between the performance phase of the task or rather the inter-trial (reset and relax) phases.

(iii) Does sustained attention improve after an inpatient multiprofessional complex treatment? If yes, is this reflected by changes in the ERPs/power spectrums of the EEG?

(iv) What are the associations between parameters of cognition, processing speed, mental fatigue, HrQoL and self-assessment of cognitive abilities, respectively, and ERPs/power spectrums of the EEG?

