Sustained attention will be measured with a 16-min cued Go-NoGo task on a computer [adapted from Pershin et al. (2023)]. Participants will see different pairs of pictures from the categories “animals,” “trees” and “fruits” (see Table 1) and have to react as fast as possible by pressing a button when two pictures with animals are shown (Go condition). In the NoGo condition, participants will see an animal as the first stimulus and a tree as the second stimulus, and have to inhibit their response (see Figure 3). The Ignore and Ignore & Novelty conditions will show two trees in a row or a tree and a fruit. No response will be required in these conditions. The presentation duration (100 ms), the interstimulus interval (1,000 ms) and the inter-trial interval will be controlled and the stimulus presentation will be randomized. Sustained attention performance in the Go-NoGo task will be quantified using several behavioral parameters. Median reaction time (RT) for correct responses in Go trials will serve as an index of sustained attentional performance. In addition, omission errors (failure to respond to Go stimuli, calculated as the proportion of missed Go trials) will be analyzed as indicators of attentional lapses, and commission errors (responses during NoGo trials, calculated as the proportion of false responses) as indicator of inhibitory control failures. Furthermore, discriminability (*d*’) will be calculated based on signal detection theory [*d*’ = Z(hit rate) – Z(false alarm rate)] to provide a bias-independent measure of sustained attention performance (Fortenbaugh et al., 2015).

**TABLE 1 T1:** The four different conditions of the Go-NoGo task.

Condition	Stimulus 1	Stimulus 2
Go	Animal	Animal
NoGo	Animal	Tree
Ignore	Tree	Tree
Ignore and novelty	Tree	Fruit

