### Data analysis and statistical approaches

2.5

Non-time series data, such as questionnaires, will be partially digitally collected and managed using the Research Electronic Data Capture (REDCap) tool hosted at the University of Kiel (Harris et al., 2009; Harris et al., 2019). REDCap is a secure, web-based software platform designed to support data capture for research studies, providing (1) an intuitive interface for validated data capture; (2) audit trails for tracking data manipulation and export procedures; (3) automated export procedures for seamless data downloads to common statistical packages; and (4) procedures for data integration and interoperability with external sources. Statistical analyses will be performed using JASP (currently Version 0.18.3) (JASP Team, 2024). We will use common descriptive and inferential statistics, as well as appropriate non-parametric statistics, to summarize the baseline data (Fortenbaugh et al., 2015). We will test for normality with Shapiro-Wilk test and Q–Q plots. To assess time-on-task effects, paired *t*-tests or Wilcoxon signed-rank tests will be used to compare reaction times and errors between the first and last quarters of the tasks (Pershin et al., 2023). In addition, correlation analyses (Pearson or Spearman) will be performed to assess the relationship between the number of trials and reaction time. Multiple linear regression will be used to analyze the influence of confounding factors (e.g., age, gender, depression, and cognitive function) on task scores.

Paired *t*-tests or Wilcoxon signed-rank tests will be used for pre-post comparisons to detect changes in clinical variables, as well as behavioral and EEG measures of sustained attention.

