### Limitations due to missing control group

3.1

The absence of a control group precludes any conclusion regarding the extent of sustained attention deficits due to mere age-related changes in sustained attention. In addition, several practical challenges may arise when implementing EEG protocols in a neurogeriatric inpatient population. Increased movement, tremor, reduced tolerance for prolonged testing, and medication effects may introduce variability into electrophysiological measures. Fatigue-related fluctuations during the computerized sustained attention tasks may also differentially affect early vs. late task phases. The clinical heterogeneity of the cohort, while increasing ecological validity, may lead to increased variance and reduced statistical power for specific subgroup effects. Moreover, the observational design limits the interpretability of results concerning potential causal inference between sustained attention, EEG parameters, and psychosocial variables.

For the subsample of participants who will be measured twice, the absence of a control group precludes a definitive conclusion regarding the extent to which any observed changes over the study period can be attributed to the complex geriatric treatment, as opposed to other potential influences, such as an extended stay in hospital or care facility in general. Additionally, even considering the generally good retest reliabilities of resting-state and task-based EEG measures, it will not be possible to causally attribute the observed changes in ERPs or power to the treatment of the participants (Näpflin et al., 2008; Vázquez-Marrufo et al., 2020; Popov et al., 2023).

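### Research question (ii) tests a phase correlation against the whole-task correlation that contains it; the shorter phase is attenuated more, which can create a false phase effect or hide a real one

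*Protocol article*

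**What the plan says.** Under research question (ii), the Introduction announces this check: "tested if the correlations observed in the initial or final phases of the task differ from those observed over the entire task duration". The correlations are those between sustained attention and EEG power in the alpha and theta bands.

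Section 2.5 handles time on task differently for behaviour. There, paired tests "will be used to compare reaction times and errors between the first and last quarters of the tasks", and those quarters are disjoint and of equal length. Section 2.5 also says that "correlation analyses (Pearson or Spearman) will be performed to assess the relationship between the number of trials and reaction time", which is a different question from comparing two correlations. Neither section 2.5 nor section 2.5.4 (Frequency-band analysis) states a phase length for the correlations or says whether behaviour is split by phase along with power.

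The Go-NoGo task lasts 16 minutes (section 2.4.2), and the Abstract says the study "will include 120 geriatric participants". Section 2.1 describes the study as exploratory.

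**The concern.** The whole-task score includes the initial and final phases and uses more data than either. A score from fewer trials carries proportionally more error, and error in either variable pulls a correlation towards zero. The phase correlation is therefore expected to be smaller than the whole-task one even if the association is constant from the first minute to the last. The null of equal correlations is then false for a reason unrelated to attention. Only a true correlation of zero or error-free measurement avoids this.

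The artefact has a fixed direction: each phase looks weaker than the whole. Early and late phases could both be reported as different when nothing changed. A late phase that truly strengthens could look no different from the whole. At stake is a mechanistic statement about when in the task EEG power tracks attention.

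**Working it through.** The article gives no alpha, effect size or reliability for this contrast, so there is no stated figure to reproduce.

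**Inputs from the article**
- n = 120 (Abstract).
- Task length 16 minutes (section 2.4.2), so a quarter is 16/4 = 4 minutes.

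**Assumptions**
- A phase is one quarter of the task. Section 2.5 uses quarters, but only for reaction times and errors.
- Power and performance are both computed per phase.
- Errors are independent between quarters.
- Quarter reliability r is the same for both measures, from 0.5 to 0.95.
- True correlation ρ is 0 to 0.4 and constant over the task.
- Tests are two-sided at 5%.

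**Step 1: expected correlations with no phase effect**

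Spearman-Brown gives the whole-task reliability: R = 4r/(1 + 3r). With equal reliability for both measures, the attenuated correlations are ρ·r for a quarter and ρ·R for the whole. For ρ = 0.40:

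| r | R | Quarter | Whole |
|---|---|---|---|
| 0.95 | 3.8/3.85 = 0.987 | 0.38 | 0.39 |
| 0.8 | 3.2/3.4 = 0.941 | 0.32 | 0.38 |
| 0.7 | 2.8/3.1 = 0.903 | 0.28 | 0.36 |
| 0.5 | 2.0/2.5 = 0.800 | 0.20 | 0.32 |

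**Step 2: how often a difference is declared with no phase effect**

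This was simulated with n = 120, four quarters and Steiger's z for dependent correlations, comparing one quarter with the whole (3,000 runs per setting; Monte Carlo standard error at most 0.9 points):

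| ρ | r = 0.95 | r = 0.8 | r = 0.7 | r = 0.5 |
|---|---|---|---|---|
| 0.2 | 6% | 8% | 10% | 11% |
| 0.3 | 7% | 13% | 17% | 21% |
| 0.4 | 9% | 22% | 28% | 36% |

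At ρ = 0 the rate is 4–5%. A separate simulation gave 6–13%, 8–22% and 11–34% for the three rows. The two agree to about two percentage points, and the second set is the one quoted in the conclusion.

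**Step 3: variations**
- Either phase may count (two looks): 8–10% at ρ = 0. With r = 0.8 to 0.7, 26–33% at ρ = 0.3 and 42–50% at ρ = 0.4. This is roughly 1.6 to 2 times the single-phase rate.
- Only power split by phase, performance from the whole task: 6–14% at ρ = 0.3 and 7–21% at ρ = 0.4.
- Fisher z treating the two correlations as independent: 0–2% at ρ = 0.3 and at most 6% at ρ = 0.4. It ignores the strong positive dependence and so overstates the standard error.

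**Step 4: masking a real effect**

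Let the true correlation rise evenly from 0.30 in the first quarter to 0.50 in the last, with r = 0.7. The average is (0.30 + 0.50)/2 = 0.40. The last quarter is expected at 0.50 × 0.7 = 0.35 and the whole at about 0.40 × 0.903 = 0.36, so the strengthening disappears. First against last would be 0.30 × 0.7 = 0.21 against 0.35.

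**Step 5: the alternative contrast**

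First against last quarter, with the same tests and no phase effect, rejects in 4.0–5.8% of runs in every setting tried, provided both quarters are equally reliable. If reliability falls from 0.8 to 0.5 in the last quarter, it rejects in about 15% at ρ = 0.3 and 24–26% at ρ = 0.4.

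**The case against.** The strongest reply is that the inflation rests on inputs the article does not give. That stands. A reader might infer that the plan will declare phase effects far more often than 5%. The article does not support this. With a true correlation near zero, or quarter reliability near 0.95 and modest correlations, the excess is small. The article's only remark on reliability is favourable, citing "generally good retest reliabilities of resting-state and task-based EEG measures", although it concerns retest rather than within-session quarters and gives no figure. Errors correlated across quarters would also reduce the bias.

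A reader might also infer that a main hypothesis is compromised. Hypothesis (ii) in the Abstract is that sustained attention correlates with EEG power. The phase contrast is a follow-up to it in an exploratory study, so no confirmatory error rate is lost.

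The missing name of a test is not a defect either, since an article commonly leaves that to the full plan. But the comparator is stated, and no choice of test makes equality the right null for a part and a whole of unequal reliability. A naive independent-samples test would mostly avoid false positives, but only by being invalid for overlapping data and insensitive.

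Finally, first against last quarter is not automatically clean. Section 3.1 itself expects fatigue to affect early and late task phases differently, and step 5 shows that unequal reliability brings the artefact back. This objection stands and shapes the fix. The other contrast in question (ii), performance against inter-trial phases, is not part-whole and is not covered by this point.

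**Conclusion.** The point holds as a conditional reliability bias. The stated contrast compares a phase with a whole that contains it and is measured more reliably, so it can report a spurious phase difference or mask a real late strengthening. With one phase equal to one quarter, both measures split, independent errors, n = 120 and a dependent-correlation test, false rejection for one phase is about 5% at true r = 0, 6–13% at 0.2, 8–22% at 0.3 and 11–34% at 0.4, for quarter reliability from 0.95 down to 0.5. It is higher if either phase may count, lower if only power is split, and mostly near 0% under an invalid independent-samples test. Severity is moderate: the likely harm is a misleading exploratory finding about timing.

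**What to change.** - Reword research question (ii) so that the tested contrast is first quarter against last quarter, as section 2.5 already does for reaction times and errors.
- Test the difference with a method for dependent correlations, for example a bootstrap that resamples participants.
- Report the whole-task correlation descriptively, without testing a phase against it.
- Report split-half reliability of power and performance for each quarter, or give disattenuated correlations as a sensitivity analysis, so that an early-late difference in measurement quality is not read as a change in association.

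The cost is one sentence in the research question, one analysis step and a reliability table, with no new data. The one loss is that the question becomes early versus late instead of phase versus overall.
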